### Random assignment to study conditions

After participants provide informed consent and enroll in the study, they will be assigned to the five study conditions (Table 1) by a random assignment of treatments in blocks produced by Stata software [39]. Recruitment will continue until the enrollment quota is met, resulting in five approximately equal-sized groups.

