#### Interactive Web Intervention (IWI)

This intervention will include targeted messages focusing on farmer-friendly techniques for adopting use of HPDs, interactive learning techniques (e.g., sound level meter), role modeling techniques (e.g., farmer testimonials), and cognitive, demonstration, persuasion techniques. Intervention delivery is not linear; participants will select the sequence of features they visit, as well as the time spent in each feature and number of visits to the site. Their patterns of use will be tracked by the enrollment and data collection systems and used in analysis.

The standard (“static”) information promoting HPD use delivered via Internet will consist of a previously developed informational brochures (i.e., *Have You Heard?* [40] and *They’re Your Ears Protect Them* [41].

The proposed study will provide a sampler of HPDs to a sub-sample of each group of farmers receiving the Interactive and Static Web Interventions and to a group of farmers who do not receive a web based intervention. The sampler will include the most commonly-used types of devices (i.e., muffs, foam plugs, pre-molded plugs, and semi-aurals).

The study will include development of the informational Web site, inclusive of elements previously developed (e.g., video testimonials and HPD insertion techniques, animated graphics). Near final systems will be tested with a sample of the target population (confirmative testing interviews). Fidelity of the intervention is assured because delivery of information via the Internet ensures a consistent presentation of the Interactive and Static interventions.

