#### Test of hypothesis 3: participants visiting the Web site more frequently will have higher HPD use than those visiting less frequently

We will assess the number of times that each individual accesses the Website and test the effect of number of views (separately for the Interactive Web Intervention and Static Web Intervention). We suspect that people with more exposures to the Website will show more impact of it (for both the Interactive Web Intervention and Static Web Intervention). However we do not expect the number of visits to be great so do not expect to have power to detect these effects. The method of analysis will depend on the distribution of number of visits. If there is little variability in number of visits this will be treated as a dichotomous predictor variable. If more variable, it will be treated as a continuous predictor. Whether significant or not, results will provide evidence about how the Interactive and Static Web Interventions work.

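### Hypothesis 3 tests the effect of self-chosen website visits and fixes in advance that any result shows how the sites work, though neither a significant nor a null result can show that

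*Protocol article*

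**What the plan says.** Under Random assignment to study conditions, only the arm is randomised: "they will be assigned to the five study conditions (Table 1) by a random assignment of treatments in blocks". Exposure to the site is left to the participant. For the interactive site, the section Interactive Web Intervention (IWI) says "participants will select the sequence of features they visit, as well as the time spent in each feature and number of visits to the site". Nothing suggests that visits to the static site are assigned either.

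The heading of Test of hypothesis 3 predicts that "participants visiting the Web site more frequently will have higher HPD use than those visiting less frequently". The text below it plans to "test the effect of number of views (separately for the Interactive Web Intervention and Static Web Intervention"), and gives the expectation: "We suspect that people with more exposures to the Website will show more impact of it". It then concedes: "However we do not expect the number of visits to be great so do not expect to have power to detect these effects". The section closes with "Whether significant or not, results will provide evidence about how the Interactive and Static Web Interventions work".

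Three other places bear on the point:
- Data analysis plan: linear mixed models with baseline as one of three times, adjusted for age and gender, plus variables on which the experimental groups differ at baseline.
- Test of hypothesis 4: the focus on interactions with time is said to be shared with the other hypotheses, so the analysis concerns change.
- Interventions: in Groups 1 and 3 the HPD sampler is supplied only after completion of the web material has been verified.

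**The concern.** The number of visits is a choice made after randomisation. A farmer who is ready to change may return to the site more often and also raise HPD use, without the visits causing the rise. The section nevertheless speaks of an effect and of impact, and its last sentence commits the authors to a mechanistic reading of whatever emerges.

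That commitment can mislead in two directions. A significant slope could be reported as the site working through exposure when it reflects who chose to visit. A non-significant slope from an analysis expected to lack power says little about how the sites work. The Discussion says that results will determine the need for program modifications such as boosters, and a finding on visit frequency could easily be cited there.

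**Working it through.** **1. The plan's own figures (Analysis and sample size estimates).** Two-sided alpha .05, 80% power, d = .43:

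n per group = 2(1.960 + 0.842)² / 0.43² = 84.9, so 85. Total 5 × 85 = 425, and 425 / (1 − 0.40) = 708.3, so 709.

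Both stated figures reproduce, but they concern randomised comparisons. None is given for Hypothesis 3. Each web format has two groups (Table 1), so 2 × 85 = 170 retained participants are available for it.

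**2. What a null could mean.** Suppose visits are dichotomised, which the section allows. Two-sample t-test, 168 df, noncentrality d·√(n₁n₂/170):

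| Split of visitors | Power, d = .43 | Power, d = .20 |
|---|---|---|
| 50/50 | 80% | 25% |
| 30/70 | 72% | 22% |
| 20/80 | 61% | 18% |
| 10/90 | 39% | 12% |

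The splits and d = .20 are assumptions. Unless the split is even and the effect as large as that planned for the randomised comparisons, a null is weak evidence. This agrees with the protocol's own concession.

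**3. What a significant result could mean.** The documents give no correlations, so these are assumed. Let visits have no effect. Let motivation correlate a with visits and b with change in use. The spurious correlation of visits with change is then r = ab. With a median split of visits, the spurious difference is r × 2√(2/π) = 1.596r SDs. Points are on the protocol's SD of .3 (30 points), assumed here to apply to change as well. Rejection rates come from 5,000 simulated trials of n = 170:

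| a, b | r = ab | Spurious difference | Rejection, split | Rejection, continuous |
|---|---|---|---|---|
| 0, 0 | 0 | 0 | 5% | 5% |
| .2, .2 | .04 | 1.9 points | 7% | 8% |
| .3, .3 | .09 | 4.3 points | 15% | 22% |
| .5, .5 | .25 | 12.0 points | 75% | 91% |

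Check for .3, .3 with continuous visits: atanh(.09) × √167 = 0.0902 × 12.92 = 1.17, and Φ(1.17 − 1.96) ≈ .21, in line with the simulated 22%.

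**4. Which safeguards reach this.** Modelling change removes stable differences in use. Age and gender do not measure motivation. The further covariates are chosen for imbalance between experimental groups, not between frequent and infrequent visitors. None addresses motivation to change.

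**5. Sampler supply.** The test is made by web format, so it pools a group assigned the sampler with one that is not (Groups 1 and 2; Groups 3 and 4). In Groups 1 and 3 someone who does not complete the web material may receive no sampler. Few visits can then go with no supplied HPDs, and modelling change does not remove this.

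**The case against.** The strongest reply is that baseline is already in the analysis. The Test of hypothesis 4 section extends the focus on change to the other hypotheses, so frequent visitors who simply used HPDs more from the outset would not create an apparent effect. That stands, and it rules out a larger figure that a reader might calculate. Take correlations of .2-.3 between visits and baseline inclination and .5-.6 between baseline and later use. The spurious correlations with the level of later use are .2 × .5 = .10, .3 × .5 = .15 and .3 × .6 = .18. With n = 170 these are significant in 25%, 50% and 65% of trials. The arithmetic is right, but it describes later use analysed without baseline. If the baseline variable is HPD use itself, with equal variances and no other path, the correlation of visits with change is −a√((1 − b)/2), where b is now the baseline-to-later correlation. That gives −.10, −.15 and −.13, against the hypothesis. A positive bias requires motivation to predict change.

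A reader might also infer that the protocol treats visits as randomised, or that motivation is bound to pass for a dose effect. The documents support neither. Only the conditions are said to be randomised, self-selection is stated openly, and the heading of the hypothesis is worded as an association. Nor does the text say that visits after 6 months will be used to explain 6-month use. Visit timing and the covariates for this analysis may properly be left to a fuller plan, so their absence is not an error.

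Finally, the concession on power already warns against reading a null as no effect. It does, but the closing sentence then takes the opposite line, and the two cannot both guide interpretation.

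**Conclusion.** The point holds as a fault in a stated rule of interpretation. Self-chosen visits cannot support the claim that the results show how the sites work, and an analysis expected to lack power cannot make a null informative. A fuller analysis plan with good covariates would reduce the first problem without curing it, and would not touch the second.

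The size and direction of the bias are unknown. With 170 per web format, no true effect, and motivation correlated .2-.3 with both visits and change in use, the false-positive rate is about 7-22% instead of 5%. It reaches 75-91% only at assumed correlations of .5. The illustration leaves out sampler supply, which could add to the bias. The consequence is confined to Hypothesis 3: Hypotheses 1, 2 and 4 rest on randomised comparisons and are unaffected.

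**What to change.** - Label Hypothesis 3 exploratory and associational.
- Relate use at each assessment only to visits made before it.
- Adjust for baseline HPD use, the baseline attitude/belief scales and HPD sampler provision, taking account of whether the sampler was in fact supplied in Groups 1 and 3.
- Report the slope for visits with its confidence interval in each web format.
- Replace the closing sentence of the section with a statement that the analysis cannot separate site exposure from motivation, and that a non-significant result is inconclusive.

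The baseline scales, visit counts and verification of web completion are already planned, so no new data collection should be needed, provided visits are logged with their dates. The price is a weaker claim for Hypothesis 3.

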#### Test of hypothesis 4. There will be no interaction between intervention delivery mode (interactive vs. Static) and the mailed HPD intervention

Analyses to test Hypothesis 4 will be conducted by a 2 (Interactive Web vs Static Web) x 2 (providing HPDs) x 3 (times: within subjects) random intercept linear mixed model. The condition of mailed HPD intervention will not be included in these analyses. As with analysis of the other hypotheses, the focus is on the interaction(s) with time. Inclusion of a pretest time in the design and analysis means that the analysis is really about changes over time. In analyses to test Hypothesis 3, the key question is whether the changes over time are different in the group that receives both the Interactive Web Intervention and HPDs than would be expected by adding the effects of Interactive Web Intervention and supply of HPDs. The significance test of the three-way interaction will test this. We hypothesize that this three-way interaction will not be significant. However a significant interaction would be interesting, too.

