**Methods/Design:**

The purpose of this project is to compare the effectiveness of several approaches to influencing hearing protector use. Approaches include: a) an interactive, predictors-based intervention delivered via the Internet; b) a static informational web site; and c) a mailed sampler of hearing protectors. The goals are to further develop an intervention to promote farmers’ use of HPDs, and compare the effectiveness of the interventions delivered in various combinations. Participants will include 701 farmers. Sites will be affiliates of a major farmer organization. Data will be collected at baseline, 6, and 12 months. A random intercept mixed model will be used to explore the fixed effects of the three NIHL prevention interventions over time while adjusting for age and gender. This project will involve a partnership between the University of Michigan and a major farmer organization to accomplish project aims.

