### Analysis and sample size estimates

Power analysis was conducted using PASS software [43] to determine the sample size needed to provide 80% power to detect important effects that we expect to see in the research, based on comparisons between conditions with alpha of .05 two tailed, given findings from past studies. Given how low use of HPDs is among farmers, we expect to produce and detect changes of 13% in percent time use between conditions with a standard deviation of .3, thus an effect size d of .43 which is a bit smaller than what Cohen (1992) defined as medium sized. A sample size of 85 per group is needed to have 80% power to detect an effect size d = .43. With a second posttest at 12 months we have allowed for a loss of up to 40%, so will recruit 709 subjects total to retain 425 or 85 per group.

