### Data analysis plan

Descriptive statistics will determine frequency distributions, percentage distributions, and means and standard deviations. Distributions of variables will be examined to detect and correct values outside of the legal range. They will also be examined for the normality of their distribution and transformed as appropriate so they meet the assumptions of the statistical analysis. Cronbach’s alphas will be used to assess internal consistency of multiple item scales as a measure of reliability. Scales with alphas of at least .63 will be considered usable. The various experimental groups will be compared on baseline values of variables. Independent variables found to differ between groups at baseline will be added to the analyses as covariates.

A random intercept mixed model will be used to explore the fixed effects of the three NIHL prevention interventions over time adjusting for age and gender as covariates. The model will include a random intercept for subjects to control for non-independence of repeated measures. A compound symmetric covariance structure will be specified in the model. Each of the outcomes: use of HPDS, attitudes, and beliefs will be modeled separately in order to investigate the effects of web interventions and mailed hearing protection devices. The data will be analyzed within two research designs. First will be the complete factorial design 2 (interactive vs. static web) x 2 (sent HPDs) x 3 (times: baseline, 6 months, and 12 months). This will not include the condition in which participants are simply sent HPDs. The second design will include all conditions in an incomplete factorial 3 (interactive web vs, static web vs. no web) X (sent HPDs) x 3 (times: baseline, 6 months, 12 months). SAS 9.3 (SAS Institute Inc., Cary, NC, USA) and SPSS 22 will be used for all analyses. A p-value of < .05 will indicate statistical significance.

#### Tests of hypotheses 1 and 2

Participants receiving interactive Web interventions will have higher HPD use and more favorable use-related attitudes/beliefs than participants not receiving Interactive Web interventions;Participants receiving the mailed HPD Intervention will have higher HPD use and more positive use-related attitudes/beliefs than participants not receiving the mailed HPD Intervention.

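### Hypothesis 4 predicts no interaction, but its only test is a significance test with no margin, so a non-significant result cannot support it

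*Protocol article*

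**What the plan says.** The heading of the Hypothesis 4 section words the hypothesis as a null: the web format (interactive or static) and the mailed protectors do not interact. The analysis is a 2 x 2 x 3 random intercept model on four of the five groups, leaving out the group that receives protectors alone. The section then fixes the test and the expected result: "The significance test of the three-way interaction will test this. We hypothesize that this three-way interaction will not be significant". It adds that a significant result would also be of interest.

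The Data analysis plan sets the threshold for all tests: "A p-value of < .05 will indicate statistical significance". It specifies compound symmetry but gives no value for the within-subject correlation.

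The section on sample size describes its power as "based on comparisons between conditions with alpha of .05 two tailed". The planning values are "we expect to produce and detect changes of 13% in percent time use between conditions with a standard deviation of .3", and the result is "A sample size of 85 per group is needed to have 80% power to detect an effect size d = .43". The article gives no power or precision figure for the interaction.

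**The concern.** A non-significant test can mean that the interaction is negligible, or that the data are too imprecise to tell. The rule for H4 does not separate the two. It also works the wrong way round: the smaller the trial or the heavier the dropout, the more likely the predicted result becomes.

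The stated power does not help, because it belongs to a different contrast. The interaction is a difference of two differences over four cells, so at equal cell size it has twice the variance of a comparison of two conditions. For Hypothesis 3 the article warns that power is not expected. For H4 it gives no such warning, and a reader could carry the 80% across.

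At stake is the conclusion on whether mailed protectors add the same benefit whichever web format is used. The H4 section itself treats departure from additivity as its key question.

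**Working it through.** **Inputs from the article.** Difference 13 points, SD 30 points, two-sided alpha .05, 85 retained per group, compound symmetry, three time points, four groups in the H4 model.

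**Assumed.** The within-subject correlation rho, shown from 0.3 to 0.8, and an interaction of the same size at 6 and 12 months.

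**1. The plan's own figure.** With d = 0.43, n per group = 2(1.96 + 0.842)²/0.43² = 84.9, so 85. Power at 85 per group is 80.0%. Recruitment is 425/0.6 = 708.3, so 709. Both figures reproduce. The abstract's total differs ("Participants will include 701 farmers"), but 701 x 0.6/5 = 84 per group changes nothing material here.

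**2. The interaction at one time point.** The contrast is (G1 - G2) - (G3 - G4).
- SE = 30 x sqrt(4/85) = 6.51 points. For two conditions, SE = 30 x sqrt(2/85) = 4.60.
- Power for 13 points: 13/6.51 = 2.00, which gives 51.5%.
- 95% half-width: 1.96 x 6.51 = 12.8 points, about the whole planned effect.
- Cell size for 80% power: 4 x (30 x 2.802/13)² = 167.2, so about 168 retained per cell.

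This takes SD 30 as the SD of the analysed quantity. For change from baseline, the SD is 30 x sqrt(2(1 - rho)), which equals 30 only at rho = 0.5.

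**3. The test as planned.** The web x protector x time interaction has 2 df. Its noncentrality is (delta/30)² x (2/3) / ((1 - rho) x 4/85). At rho = 0.5 and delta = 13 this is 0.1878 x 0.6667 / 0.02353 = 5.32. Power from the noncentral F with 2 and 672 df:

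| rho | 13-point interaction | 6.5-point interaction |
|---|---|---|
| 0.3 | 40% | 13% |
| 0.5 | 53% | 16% |
| 0.7 | 76% | 25% |
| 0.8 | 91% | 35% |

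**4. Sensitivity.**
- If the interaction is 6.5 points at 6 months and 13 at 12 months, power is 31%, 41%, 63% and 81% at the same correlations.
- If nobody were lost (709/5, so 141 per cell), power for a constant 13 points would be 60%, 76%, 94% and 99%.

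**5. A different estimator.** Averaging the two follow-ups with baseline adjustment gives SE = 30 x sqrt((1 - rho)(1 + 2rho)/2 x 4/85), which is 4.60 at rho = 0.5. A two-sided .05 test of 13 points then has power Phi(13/4.60 - 1.96) = 81%. The corresponding figures are 76% at rho = 0.3 and 91% at rho = 0.7. A power figure for H4 therefore has no meaning until the estimator and the correlation are named.

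**The case against.** The strongest reply is that the article only records an expectation, describes its model as exploratory, and says that a significant interaction would be interesting too. Several stronger readings are tempting, and the text does not support them.

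- **That the trial will claim additivity.** The article does not say so. It gives no rule for how a non-significant result will be reported.
- **That power is only about 50%.** This holds near rho = 0.5. The correlation is not given, and at about 0.75 or above the planned test passes 80% for a constant 13-point interaction.
- **That the article claims 80% power for H4.** It ties the figure to comparisons between conditions and does not extend it to the interaction.
- **That use of the protectors-only group rests on H4.** Both the complete and the incomplete factorial are specified unconditionally, and no term is said to be dropped if non-significant. The tests of Hypotheses 1 and 2 do not wait for the result of H4.

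It is also fair that an article may leave a margin to a fuller document. That does not remove the point, because the article does fix the test for H4, and the test it fixes cannot support the hypothesis as worded. This holds at any power.

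**Conclusion.** The point holds in a limited form. H4 is a null hypothesis whose only stated test is a significance test with non-significance predicted, and such a result would not show that an important interaction is absent. That conclusion needs no assumption about power.

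The size of the problem depends on the unstated correlation. Over 0.3 to 0.8, with 85 per cell, SD 30 and compound symmetry, the planned test has 40% to 91% power for an interaction as large as the whole planned effect. For half that effect it has 13% to 35%. Even at the favourable end, a 6.5-point interaction would be missed about two times in three. The sample-size statement is correct for what it covers, and it does not cover H4.

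**What to change.** 1. In the H4 section, report (G1 - G2) - (G3 - G4) in change in HPD use with its confidence interval, and state that non-significance will not be read as no interaction.
2. Conclude that there is no important interaction only if the 90% interval lies inside a margin that the sponsor states in advance and justifies. The margin should be smaller than 13 points, because a margin equal to the whole planned effect would let through an interaction as large as the effect the trial was sized to find. Otherwise report H4 as inconclusive. Labelling H4 exploratory is an acceptable alternative.
3. In the section on sample size, state that the 80% applies to comparisons of two conditions and not to H4. Give any power or precision figure for H4 for the estimator actually used, with its assumed correlation.

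The cost is a few sentences and no participants. The downside is that H4 may well end as inconclusive. At rho = 0.5 the 90% half-width is 1.645 x 6.51 = 10.7 points for change at a single follow-up, or 1.645 x 4.60 = 7.6 points for the baseline-adjusted average. A margin below the half-width could not be met even by an estimate of exactly zero.
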